### Data collection

Data will be collected from medical records (where possible), participant interviews in person and by telephone, physical assessments, and calendars mailed to the research centre. Participants will undergo two home-based assessments; one prior to randomisation and the other 12 months after randomisation. A physiotherapist or a trained research assistant who is unaware of group allocation will perform the assessments. Each assessment will take about one hour to complete.

Details of fracture, comorbidities and hospital stays will be obtained from the medical records where possible. From participant interviews we will obtain baseline information on pre-fracture daily task independence, fracture details, medical conditions, cognition (using the Short Portable Mental Status Questionnaire) [33], nutrition (Mini Nutritional Assessment) [34], medications, and fracture interventions (including surgical fixation, occupational therapy home visits and physiotherapy). The primary and secondary outcomes will be administered at baseline and 12-month assessments.

All participants will receive 12 one-month calendars and questionnaires at the time of the baseline assessment. Participants will be asked to record falls (primary outcome) and use of health and community services on the calendars and to return completed calendars in pre-paid envelopes to the research centre each month. If calendars are not returned, participants will be telephoned to ask about their fall history for that month. Any fall reported on the calendars will be followed up with a phone call to obtain further information about the details and consequences of the fall. All participants will be telephoned at three, six, nine and twelve months for assessment of the Boston University Activity Measure for Post Acute Care (AM-PAC; primary outcome) [35], and European Quality of Life-5 dimensions quality of life assessment (EQ-5D-5 L; secondary outcome) [36]. Staff who receive calendars and questionnaires, make follow up phone calls and enter data will be unaware of group allocation.

### Outcome measures

#### Primary outcome measures

The primary outcomes measured are mobility-related disability and rate of falls. Mobility-related disability will be assessed in three ways: 1) the performance-based Short Physical Performance Battery (SPPB) [37], 2) the self-reported AM-PAC, 3) the self-reported Late Life Functioning and Disability Instrument, Disability Component (LLFDI-DC) [38].

The SPPB examines the ability to stand (for 10 sec) with the feet together in the side-by-side, semi-tandem, and tandem positions; time taken to walk four metres; and time to rise from a chair and return to the seated position five times. The data will be analysed using the lower extremity continuous summary performance score (CSPS) [39]. The activity limitation component of disability will be measured with the computerised version of the AM-PAC, using the basic mobility and daily activity components. The LLFDI-DC will measure the participation restriction element of disability [38].

The number of falls will be assessed using monthly calendars and follow-up telephone calls as required. A fall is defined using the Kellogg definition as an incident where the body unintentionally comes to rest on the ground or another lower level that is not the result of a loss of consciousness, violent blow, or sudden onset of paralysis such as stroke or an epileptic seizure [40].

#### Secondary outcome measures

Secondary outcome measures will be balance and mobility, falls risk, physical activity, walking aid use, frailty, pain, nutrition, falls efficacy, mood, positive and negative affect, quality of life, assistance from others, hospital readmission, and health-system and community-service contact. These measures aim to increase understanding of the effects of the program on the aspects that contribute to an older person’s capabilities and quality of life, and to enable us to conduct economic analyses. The secondary outcomes are described in Table 1. The overall results will be available to participants upon publication of the trial outcomes. Participants will be given their own results if requested; we anticipate participants will express their interest in receiving this information at their 12-month outcome assessment.

**Table 1 Tab1:** Secondary outcome measures

Domain	Assessment	Description
Balance and mobility	Coordinated stability test [53]	Measures ability to adjust body position in a controlled manner when near the limit of the base of support.
	Maximal balance range test [53]	Measures the maximum distance participants can lean backward and forward.
	Step Test [54]	Dynamic single limb stance is assessed by counting the number of times the participant is able to step one foot on, then off, a 7.5 cm block as quickly as possible in 15 seconds.
	Short Physical Performance Battery (SPPB), individual components	The SPPB components are the ability to stand (for 10 sec) with the feet together in the side-by-side, semi-tandem, and tandem positions; time taken to walk four metres; and time to rise from a chair and return to the seated position five times.
	Choice stepping reaction time [55]	Time to complete a standardised stepping routine onto four white squares on a portable mat, while standing.
Falls and fall risk	Fallers	Proportion of fallers (people having one or more falls) over the 12-month follow-up period.
	Injurious falls and fractures	Number of falls requiring medical attention and fractures over the 12-month follow-up period.
	Physiological Profile Assessment (PPA) summary score and individual components [53, 56]	Includes five measures of physiological functioning (knee extension strength, postural sway, reaction time, lower limb proprioception and visual contrast sensitivity).
Physical activity	Incidental and Planned Exercise Questionnaire [57]	Level of physical activity relating to both basic and more demanding activities is assessed with a 10-item questionnaire.
Walking aid use	Use of walking aid	The use and type of walking aid is recorded both indoors and outdoors.
Frailty	6-point scale based on the Fried criteria [58]	Frailty is measured using five criteria: unexplained weight loss, grip strength, exhaustion, walking speed, activity level.
Pain	6-point numeric rating scale	The participant selects a whole number that best reflects the intensity of their pain.
Nutritional status	Mini Nutritional Assessment [34]	Screens for, and assesses, malnutrition in older people.
	Body mass index	Bodyweight in kilograms divided by height in metres squared.
Fall-related self-efficacy	Questions about self-rated fear of falling and balance	Participants are asked to rate their perceived balance and their fear of falling on 5-point ordinal scales
	Short version of the Falls Efficacy Scale-International [59]	Level of concern about falling during a range of activities is rated on a 4-point scale.
Mood	Five-item version of the Geriatric Depression Scale [60]	Screens mood in older people. The five-item Geriatric Depression Scale is comparable with the 15-item version in terms of psychometric properties.
Positive and negative affect	Positive and Negative Affect Scale [61]	Two 10-item scales that measure positive and negative affect.
Health-related quality of life	European Quality of Life-5 dimensions (EQ-5D-5 L) [36]	A standardised measure of health status that provides utility weights to allow calculation of quality adjusted life years (QALYs) for use in the economic evaluation [62].
	Short Form 12-item Survey (SF-12) Version 2 [63]	A 12-item questionnaire that measures functional health and well-being.
Assistance from others	Three questions about assistance received	Establishes the presence of, and reason for, assistance from agencies, family or friends.
Hospital re-admission	Number of hospital readmissions and days in hospital during the follow-up period	Ascertained via the same calendars used for falls follow-up over the first 12 months of the study, follow-up phone calls for missing calendars and contact with carers if contact is lost with the participant. At 2 and 4 years after randomisation, data linkage will be undertaken via the New South Wales Centre for Health Record Linkage (NSW CHeReL) to seek information regarding mortality and hospital admissions.
Health-system and community-service contact	Number of contacts with health and community services	Collected on a monthly basis along with the falls calendars. Inpatient hospital and emergency department contact will be assessed using data linkage via the NSW CHeReL. Data will also be used in economic analyses.
The stage of motivational readiness for change	Physical Activity Stages of Change Questionnaire [48]	The 4-item questionnaire measures the stage of readiness to change and self-efficacy to exercise.

#### Adverse events

An adverse event is defined as an incident resulting in harm to a person receiving health care [41]. The event may or may not be related to the intervention, but it occurs while the person is participating in the intervention; that is, while they are doing exercise or physical activity. For the purpose of this trial, a serious adverse event is defined as an unwanted and usually harmful outcome (e.g., fall, seizure, cardiac event). A minor adverse event will be defined as musculoskeletal soreness that interferes with activities of daily living for more for 48 hours or requires medical attention [42]. Adverse events will be monitored in the intervention group via calendars and during visits by the treating physiotherapist.

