### Secondary objectives

To compare the effect of an exercise and fall prevention self-management program versus usual care on balance and mobility, falls risk, physical activity, walking aid use, frailty, pain, nutrition, falls efficacy, mood, positive and negative affect, quality of life, assistance from others, hospital readmission, and health-system and community-service contact in older people with a recent fall-related lower limb or pelvic fracture.To establish the cost-effectiveness and cost-utility of the intervention approach, compared with that of usual care, from the perspective of the health and community care funder.To describe the safety and tolerability of the program.To determine features associated with uptake of the intervention.

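### The serious adverse event definition does not require harm and is not graded by consequence, so an uninjured fall during exercise can count as serious although it is not an adverse event

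*Protocol article*

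**What the plan says.** The Adverse events section of the protocol article gives three definitions and one monitoring rule.

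- Adverse event: "An adverse event is defined as an incident resulting in harm to a person receiving health care". No causal link with the program is needed. The timing condition reads: "it occurs while the person is participating in the intervention; that is, while they are doing exercise or physical activity".
- Serious: for this trial, "a serious adverse event is defined as an unwanted and usually harmful outcome (e.g., fall, seizure, cardiac event".
- Minor: "musculoskeletal soreness that interferes with activities of daily living for more for 48 hours or requires medical attention".
- Monitoring: "Adverse events will be monitored in the intervention group via calendars and during visits by the treating physiotherapist".

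Three other places bear on these definitions. Under Primary outcome measures, a fall is "an incident where the body unintentionally comes to rest on the ground or another lower level", with exclusions for causes such as loss of consciousness; injury is not a condition. Table 1 lists a secondary outcome that is graded by consequence: "Number of falls requiring medical attention and fractures over the 12-month follow-up period". The Secondary objectives include this one: "To describe the safety and tolerability of the program".

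**The concern.** A serious adverse event should be an adverse event with a grave consequence. Here the serious class is wider than the parent class on harm, and it is marked out by kind of event rather than by what happened to the participant. The criteria that do describe a consequence sit in the lower class.

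What is at stake is the safety objective. The Adverse events section is the only text in the article that defines and grades adverse events. The Discussion reports that an earlier trial of the same exercise program, in people recently discharged from hospital, found a significantly higher fall rate in the intervention group. Readers will therefore look closely at the serious events here. A list that puts a harmless fall beside a cardiac event, and repeats falls already counted in the primary outcome, would not tell them how much serious harm occurred.

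**Working it through.** No arithmetic applies: the article gives no adverse event rate or count to reproduce. The check is to compare the definitions and then apply them to cases.

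**Comparison**

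1. Harm: required for an adverse event, only usual for a serious one. The serious class as worded therefore admits harmless events and is not contained in the adverse event class.
2. Falls: named as a serious event without a qualifier. The trial's own fall definition needs no injury, so the example does not bring the harm condition back.
3. Consequence: the serious definition has none. The minor definition has two, namely interference with daily activities lasting beyond 48 hours, or a need for medical attention.
4. Coverage: the minor class names soreness only, and the section offers no class besides serious and minor.

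**Application to events during exercise**

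| Event | Adverse event? | Serious as worded? | Minor? |
|---|---|---|---|
| Fall, no injury | No, no harm | Yes, a listed example | No |
| Fall with fracture | Yes | Yes | No |
| Harmful cardiac event | Yes | Yes | No |
| Soreness needing medical attention | Yes, taking soreness as harm | The words fit | Yes, by name |
| Skin tear without lasting effect | Yes | Only class available | No |

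Row 1 is the contradiction: serious, but not an adverse event. Row 4 shows that the two classes overlap, and that a consequence needing care is assigned to the lower one. Row 5 shows that a mild harm can be recorded only as serious, or not at all. Rows 1 and 2 share a class, so the class does not measure severity.

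**The case against.** The strongest reply is that the definitions are nested: the section defines an adverse event first, so a serious one must meet that definition, and an uninjured fall drops out. This is a natural reading, and it means one cannot say that uninjured falls will certainly be counted as serious. But the article does not state the nesting, and the word usually would then serve no purpose. Two readings that give different counts still need reconciling. Nesting also supplies no consequence criterion and no class for mild harms other than soreness.

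A second reply is that the definition is deliberate, and that counting falls during exercise cautiously is reasonable after the earlier excess of falls. That supports reporting such falls. It does not support grouping them with serious harm. Nor is this detail that an article leaves to a fuller document: the rule is stated, as one made for this trial.

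Several stronger inferences are tempting, and the article does not support them.

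- *The serious count would not measure harm at all.* Seizures, cardiac events and injurious falls would be counted. The fault is mixing. The article also promises no serious-event count as such, only a description of safety.
- *Musculoskeletal injury is graded as minor.* The text says soreness. A sprain or fracture is not named there.
- *Serious harms could not be told apart from harmless falls.* Under Data collection, every fall reported on a calendar is followed by a call about its consequences. Table 1 separately records falls needing medical attention, fractures, and hospital readmissions and days.
- *Most of the serious list would be harmless falls.* Assumed rates can produce such a figure. At 1.5 falls per person-year, 175 x 1.5 = 262.5 falls; if 10% to 50% occur during activity, about 26 to 131 enter the list. Only the 175 comes from the article. Assuming further that 10% to 30% need medical attention leaves 70% to 90% that do not, but that is not the share without injury, since a bruise is harm. These figures do not size the problem.

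**Conclusion.** The point holds as a contradiction and a grading fault in a stated rule. The serious class does not require the harm that an adverse event requires, it is not separated from the minor class by consequence, and the two classes neither exclude each other nor cover all harms. A serious-event summary built on it would mix harmless and harmful events and would not measure severity.

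The effect is confined to adverse event reporting. The primary and secondary efficacy analyses and the sample size do not depend on these definitions. Adverse events are monitored in the intervention group, so no between-group comparison of them is at issue. No numerical size can be given from the article.

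The conclusion assumes that the definitions are applied as printed. If sites used the nested reading, uninjured falls would not be counted as serious, but the lack of grading and the gap for mild harms would remain. The point should be corrected because safety is a stated objective, though it does not threaten the trial's main conclusions.

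**What to change.** Reconcile the definitions in the Adverse events section:

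- State that a serious adverse event is an adverse event, so harm and the timing condition apply to it.
- Separate serious from non-serious by consequence and not by type of event, for example death, hospital admission, fracture or lasting loss of function.
- Class every other harm as non-serious, including soreness and mild injuries of any kind.
- Report uninjured falls during exercise on a separate line, outside the serious count.

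For falls and admissions, the consequences are already due to be collected through the fall follow-up calls and the injurious-fall and readmission outcomes in Table 1. No new assessment is needed for these.

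The cost is a reworded definition and the re-grading of events already logged. For events that are not falls, nothing in the article shows that the consequence is always recorded, so the physiotherapist's or calendar record must note it. Where it was not noted, the event should be shown as ungraded.

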## Discussion

Many people who have suffered a lower limb fracture are left with long-term disability and increased risk of future falls, however there is no clear evidence for a successful and cost-effective program to reduce mobility-related disability and falls in fracture survivors. This randomised trial will determine whether a 12-month home exercise and falls prevention self-management program reduces mobility-related disability and falls among older men and women who live in the community following a lower limb or pelvic fracture. There will be far-reaching benefits for older people, their carers and the community if this program can assist in minimising mobility-related disability and falls in this high-risk population.

A strength of this study is that the intervention program could be delivered as part of routine care. While the program does not have as much contract with health professionals as interventions previously shown to be successful in increasing mobility after hip fracture [10, 11], we believe it is sufficiently intense to be effective, yet inexpensive enough to be implemented in real-life healthcare systems. The novel intervention combines an individualised exercise program with a self-management approach and is based on the highest level of evidence for the prescription of exercise for older people. The exercise component, the WEBB program, was designed using evidence from systematic reviews and randomised trials that have demonstrated improved strength, balance and mobility in older people. The WEBB program increases mobility in older people with frailty [49], Parkinson’s Disease [50], stroke [51], and recent hospitalisation [22]. Of concern, in our previous trail of the WEBB program in older people recently discharged from hospital the rate of falls was statistically significantly greater in the intervention group compared to the control group.^22^ The reason for increased falls is unclear, however it may be that home exercise as a single intervention may be insufficient to reduce falls in this high-risk post hospital population. The addition of the fall prevention component in the current study addresses this finding by specifically targeting fall risk and falls self-efficacy.

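### Adverse events are monitored in one arm only and only during activity, so limiting soreness, and cardiac events or seizures without hospital contact, can be listed but not compared with controls

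*Protocol article*

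**What the plan says.** All of the following is in the protocol article.

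- **Who is monitored** (Adverse events): "Adverse events will be monitored in the intervention group via calendars and during visits by the treating physiotherapist". No such monitoring is described for controls.
- **When an event counts** (Adverse events): "it occurs while the person is participating in the intervention; that is, while they are doing exercise or physical activity". Relatedness is not required.
- **Grades** (Adverse events): "a serious adverse event is defined as an unwanted and usually harmful outcome (e.g., fall, seizure, cardiac event" is one grade. The other begins: "A minor adverse event will be defined as musculoskeletal soreness that interferes with activities of daily living", and requires either a duration above 48 hours or a need for medical attention.
- **Objective** (Secondary objectives): "To describe the safety and tolerability of the program".
- **Calendars** (Data collection): every participant gets 12 monthly calendars for falls and service use, and is telephoned at three, six, nine and twelve months. "Staff who receive calendars and questionnaires, make follow up phone calls and enter data will be unaware of group allocation".
- **Earlier trial** (Discussion): in a previous trial of the same exercise programme, "the rate of falls was statistically significantly greater in the intervention group compared to the control group".

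**The concern.** An event count from one arm cannot be attributed to the programme. The participants are aged 60 or over and have had a fracture within two years, so some soreness and some cardiac events are to be expected without any intervention. With no count from controls, the reader cannot tell whether the programme's figure is high, ordinary or low.

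This is a rule about which data are collected. A statistical analysis plan could not repair it, because events never asked about cannot be analysed later.

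Two secondary matters follow from the same section. The time window and the minor-event definition do not fit each other. The use of calendars for intervention-arm events also sits awkwardly with the statement that calendar staff do not know the allocation.

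**Working it through.** The plan gives no figure for adverse events, so there is none to reproduce. The check sets the passages side by side and adds two small calculations that bound the concern.

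**1. Which harms have a control comparator**

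| Harm | Intervention arm | Control arm | Source |
|---|---|---|---|
| Falls, proportion of fallers | yes | yes | Data collection; Outcome measures; Table 1 |
| Falls needing medical care, fractures | yes | yes | Table 1 |
| Pain (baseline and 12 months) | yes | yes | Table 1; Data collection |
| Readmissions, hospital days, emergency contact | yes | yes | Table 1 |
| Deaths (record linkage at 2 and 4 years) | yes | yes | Table 1 |
| Soreness limiting daily life | yes | no | Adverse events |
| Cardiac event or seizure without hospital contact | only if during activity | no | Adverse events |

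The last two rows are the gap. Monitoring covers up to 175 of the 350 participants and none of the other 175. Contacts with health services are counted in both arms, but Table 1 describes a number of contacts, not their cause, so they do not fill those rows.

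**2. Does the definition hold together?** A session is 20 to 30 minutes. Soreness that must last more than 48 hours cannot lie within a session; at most it can begin in one. The general definition requires occurrence during activity and does not say whether onset is meant. On a literal reading, soreness that first appears after a session is a minor event under one sentence and no event under the other.

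**3. Calendars and blinding.** The Data collection section lists only falls and service use as calendar entries; the Adverse events section adds adverse events for one arm. There are two readings:

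- Only intervention calendars carry such entries. An entry then reveals the arm to staff who are meant not to know it.
- All calendars can carry them. Control data are then obtainable, and the restriction to one arm discards them.

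The article does not say which applies.

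**4. How narrow is the time window?** The prescribed sessions take 3 × 20 to 3 × 30 = 60 to 90 minutes a week. A week has 168 × 60 = 10,080 minutes, so the share is 60/10,080 = 0.6 % to 90/10,080 = 0.9 %. This is a floor, not the coverage, because the definition also includes physical activity, whose duration is not given.

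**5. Can the trial show an increase in falls?** The Sample size calculation states 80 % power for a rate ratio (IRR) of 0.70, but gives neither the control fall rate nor the dispersion, so that figure can be neither reproduced nor refuted. I assumed a control rate μ of 0.8 to 2.0 falls per year, dispersion k of 0.5 to 2.0, one year of follow-up and a two-sided 5 % test, with

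variance of log IRR = (1/μ + k)/n + (1/(μ·IRR) + k)/n

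power = Φ(|log IRR|/√variance − 1.96)

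| n per arm | IRR 0.70 | IRR 1/0.70 = 1.43 |
|---|---|---|
| 175 | 0.43 to 0.89 | 0.48 to 0.93 |
| 149 (175 × 0.85, after 15 % dropout) | 0.38 to 0.83 | 0.42 to 0.89 |

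Example with n = 175, μ = 2.0, k = 0.5 and IRR 1.43: variance = (1.00 + 0.85)/175 = 0.01057; 0.3567/0.1028 − 1.96 = 1.51; power = 0.93. At every assumed setting, power for the increase exceeds power for the decrease of the same ratio.

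**The case against.** The strongest reply is that the important harms are already compared between arms, and that the safety objective is descriptive. Most of this stands, and it rules out several stronger readings.

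- A reader might infer that the trial cannot compare harm between arms at all. It can: the first five rows of the table are collected without restriction by arm, and the Statistical analysis section names a negative binomial comparison of fall rates and a relative risk for fallers.
- A reader might infer that the danger seen in the earlier trial will go unseen here. That danger was falls, which are a primary outcome in both arms, and step 5 shows that an increase is at least as detectable as a decrease. The earlier result shows that harm is plausible, not that this harm is missed.
- A reader might infer that the safety objective is unanswerable. It asks only for a description, which monitoring of programme recipients can supply. What it cannot supply is attribution.
- A reader might infer that a fracture or admission soon after a session is lost. Both are counted elsewhere, at any time and in both arms. A harmless stumble during exercise is not a serious event either, because the general definition first requires harm.
- A reader might infer that the calendars unblind the falls data. Calendar items that differ by arm are an inference, not something the article states. The article also acknowledges that falls are self-reported and that differential reporting is a limitation.

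The reply does not remove the last two rows of the table. It does not reconcile the time window with the 48-hour criterion, or the calendar route with the blinding statement.

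**Conclusion.** The concern holds in a limited form and should be fixed. Adverse events as this protocol defines them are collected in one arm and within a restricted window. Limiting soreness, and cardiac events or seizures without hospital contact, can therefore be described but not compared with a background rate. Evidence on harm between arms is confined to falls, falls needing medical care, fractures, pain, hospital and emergency use, and linked mortality. That is substantial, which is why the matter is not more serious.

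The conclusion rests on reading the monitoring sentence as limiting collection to the intervention group, which is its plain sense. The two conflicts of wording are calls for reconciliation; neither shows that the primary falls comparison is biased.

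**What to change.** - Ask the same adverse-event questions of both arms, covering any time in the 12 months, through the monthly calendars and three-monthly calls that already reach everyone, and compare the answers by arm.
- Keep events during exercise sessions as a separate descriptive list for the intervention arm, recorded by the physiotherapist on a form that does not pass through the blinded calendar staff. State that this list does not feed the primary falls count, since a fall is both an example of a serious event and a primary outcome.
- Reconcile the occurrence-during-activity rule with the 48-hour soreness criterion, and the calendar route with the statement that calendar staff are unaware of allocation.
- The Timeframe section has follow-up ending in December 2015. Where it is complete, present injurious falls, fractures, admissions and deaths by arm as the safety comparison, using the calendar data and the linkage where it has been run. Label the events in the Adverse events section as uncontrolled and descriptive.

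The cost is one or two extra calendar or call items, a separate form and slightly more data handling. If follow-up is over, it is a table from data already held or already planned.
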